## Abstract

**Background:**

Preterm labour is the main cause of perinatal morbidity and mortality in the Western world. At present, there is evidence that tocolysis for 48 hours is useful in women with threatened preterm labour at least before 32 weeks. This allows transfer of the patient to a perinatal centre, and maximizes the effect of corticosteroids for improved neonatal survival. It is questionable whether treatment with tocolytics should be maintained after 48 hours.

**Methods/Design:**

The APOSTEL II trial is a multicentre placebo-controlled study. Pregnant women admitted for threatened preterm labour who have been treated with 48 hours corticosteroids and tocolysis will be eligible to participate in the trial between 26^+0 ^and 32^+2 ^weeks gestational age. They will be randomly allocated to nifedipine (intervention) or placebo (control) for twelve days or until delivery, whatever comes first.

Primary outcome is a composite of perinatal death, and severe neonatal morbidity up to evaluation at 6 months after birth. Secondary outcomes are gestational age at delivery, number of days in neonatal intensive care and total days of the first 6 months out of hospital. In addition a cost-effectiveness analysis will be performed. Analysis will be by intention to treat. The power calculation is based on an expected 11% difference in adverse neonatal outcome. This implies that 406 women have to be randomised (two sided test, β 0.2 at alpha 0.05).

**Discussion:**

This trial will provide evidence as to whether maintenance tocolysis reduces severe perinatal morbidity and mortality in women with threatened preterm labour before 32 weeks.

**Trial Registration:**

Clinical trial registration: , NTR 1336, date of registration: June 3^rd ^2008.

## Background

Preterm birth is the most common cause of neonatal morbidity and death worldwide [1]. Two thirds of the preterm births occur as a result of spontaneous labour beginning with spontaneous contractions or with preterm rupture of membranes. Preterm birth accounts for approximately 75% of all neonatal deaths and 50% of childhood neurological morbidities [2]. Moreover, it is associated with high immediate and long-term costs after discharge from the hospital [3]. These include costs for special education services and institutionalised care for physically and mentally disabled infants [4]. The prevalence of adverse neonatal outcome is strongly related to gestational age at delivery and declines from 77% at 24-27 weeks to less then 2% at 34 weeks and beyond [5]. Perinatal death and morbidity are not only strongly related to early gestational age but also to whether or not antenatal corticosteroids are administered [6] and whether a preterm infant is transferred to a tertiary care centre before or after birth. Postponing delivery for 48 hours with tocolytics in order to allow maximal effect of maternal parenteral steroid administration and transfer of the mother to a centre with Neonatal Intensive Care Unit (NICU) facilities is therefore standard treatment in women with the diagnosis of threatened preterm labour before 32 weeks gestational age [7].

Approximately 75% of women with a diagnosis of threatened preterm labour have not delivered after the first 48 hours of tocolytic therapy with nifedipine. After this 48 hour period the risk of preterm delivery persists. Two weeks after treatment for threatened preterm labour with nifedipine 65% of women are still pregnant [8].

Fetal fibronectin can be helpful in selecting women at risk for preterm delivery. Management based on knowledge of fetal fibronectin results significantly reduces preterm delivery less than 37 weeks compared to management without knowledge of these results (RR 0.54, 95% confidence interval 0.34 to 0.87). However the incidence of preterm delivery less than 34, 32 and 28 weeks were similar in both groups [9].

In national and international guidelines, a uniform treatment of threatened preterm delivery after 48 hours of tocolytic therapy has not yet been developed. Some obstetricians maintain tocolytic therapy until term, 37 weeks gestational age, whereas others stop tocolytics after 48 hours irrespective of gestational age or continue until for example 28 weeks gestational age. Maintenance treatment with several tocolytic agents has been being carried out in daily practice and include betamimetics [10,11], magnesium sulphate, indomethacin and calcium channel blockers [12] in order to achieve further prolongation of pregnancy and improvement of neonatal outcome. At present, no beneficial effect on perinatal outcome of such prolonged treatment has been established [13]. On one hand, tocolytic maintenance therapy with calcium channel blockers might be beneficial due to a positive effect on gestational age and possibly on neonatal outcome. On the other hand, use of tocolytics is associated with rare but severe side effects on mother and child [14,15], and may increase the risk of some perinatal complications - including intra-uterine infection.

Two systematic reviews included in DARE [16,17] and the Cochrane systematic review on maintenance tocolysis with nifedipine [12] reported only a few studies on the subject, and no reliable statement on the effectiveness of tocolytic maintenance therapy (TMT) on neonatal outcome. Although nifedipine maintenance therapy may increase gestational age at delivery, there has been no improvement in neonatal or maternal outcome [18-20].

In summary, preterm delivery is an important health care problem. Whereas it is evident that tocolysis with administration of corticosteroids for 48 hours is effective, there is insufficient evidence for a uniform policy after these 48 hours. In this randomised clinical trial we will investigate the effectiveness of maintenance therapy with nifedipine compared to placebo therapy in women with a gestational age below 32 weeks. Additional data will be collected for post-hoc evaluation of the clinical relevance of cervical length measurement and the presence of fibronectin in cervical mucus prior to maintenance tocolytic therapy.

This study is conducted within the Dutch Obstetric Consortium, a collaborative effort of obstetric clinics in The Netherlands to perform clinical trials. All ten Dutch perinatal centres with NICU facilities will participate in this trial.

## Methods/Design

### Aims

The aim of this study is to evaluate the effectiveness of tocolytic maintenance therapy on perinatal outcome after initial standard 48-hours' tocolytic therapy in women with threatened preterm birth between 26^+0^-32^+2 ^weeks gestational age. The outcome is measured in terms of neonatal mortality and composite neonatal morbidity (chronic lung disease, severe intraventricular haemorrhage, periventricular leucomalacia, proven sepsis and necrotising enterocolitis), gestational age at delivery and costs.

### Participants/eligibility criteria

Women with threatened preterm delivery with a gestational age between 26^+0 ^and 32^+2 ^weeks who have not delivered after 48 hours of tocolytics and corticosteroids are eligible for participation in the APOSTEL II-trial. Women with both singleton and multiple gestations are included. We chose not to include women with a gestational age between 24 and 26 weeks to prevent protocol violation (rescue tocolysis during study medication).

Maternal exclusion criteria are signs of intrauterine infection, placenta praevia, maternal disease requiring delivery (i.e. HELLP syndrome or preeclampsia), maternal hypertension and contraindications for the use of nifedipine. Fetal exclusion criteria are signs of fetal distress (abnormal cardiotocogram, abnormal biophysical profile), serious congenital defects and intrauterine death.

### Procedures, recruitment, randomisation and collection of data

The research nurse and/or the staff of participating hospitals will identify eligible women. After the patient has given informed consent for participation in the study, she is randomised using an internet-based procedure. Randomisation is 1:1 for nifedipine or placebo.

At study entry baseline demographics, obstetric and medical history are recorded. For post-hoc analysis on a subset of women, at study entry cervical length is measured by transvaginal ultrasound and a vaginal swab is taken for fibronectin testing. Fibronectin will not be tested in women with ruptured membranes, more than 3 cm dilatation or vaginal bleeding. Fibronectin swabs are stored and analyzed after the patient has delivered. All data are collected, coded and processed with adequate precautions to ensure patient confidentiality.

### Interventions

Patients are allocated to nifedipine or placebo for twelve days. Start of study medication is 48 hours after start of the initial tocolysis. Initial tocolysis is provided according to local protocol, usually this will be Nifedipine or Atosiban. Study medication consists of 20 milligrams nifedipine every six hours, administered orally, resulting in a total daily dose of 80 milligrams, or placebo. The medication is phased out from day 10 (total daily dose 60 milligrams nifedipine) till day 12 (total daily dose 20 milligrams nifedipine) and discontinued on day 13.

After randomisation the medication package is stored by the patient herself. The administration of the study medication is noted in a schedule that is kept both by the patient and in her medical record. Non-compliance is defined as a delay in administration of studymedication of more than 6 hours.

### Follow up of women and infants

All details of delivery, maternal assessments and admissions during pregnancy are recorded in an electronic case report form (CRF). Details of neonatal admissions are also recorded. Long-term follow up of children is depending on future funding.

### Outcome measures

The primary outcome measure is neonatal mortality and a composite of neonatal morbidity. The composite morbidity rate contains chronic lung disease, severe intraventricular haemorrhage more than grade 2, periventricular leucomalacia more than grade 1, proven sepsis and necrotising enterocolitis at six months after birth.

Secondary outcome measures are gestational age at delivery, birth weight, days on supported ventilation and additional oxygen, length of admission in neonatal intensive care, total days in hospital until three months corrected age and costs. Moreover, we will compare the number of days that each neonate surpasses outside the hospital within the first 6 months after the calculated term date.

### Statistical issues

#### Sample size

The sample size is calculated based on an 11% reduction in the primary outcome 'composite neonatal morbidity', from 25% to 14%. Using a two-sided test with an alpha of 0.05 and a power of 0.80 we have to randomise 406 patients (203 in each arm).

#### Data analysis

Data will initially be analysed according to the intention-to-treat method. First, the nifedipine and placebo groups will be compared. Relative risks and 95% confidence intervals will be calculated for the relevant outcome measures.

Planned subgroup analysis will be performed to assess the consistency of a treatment effect among various patient characteristics i.e. cervical fibronectin status, presence of ruptured membranes, multiple pregnancy as well as cervical length at study entry. We will test for interaction between these characteristics and treatment effect.

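### Gestational age at entry has no stated role in the main comparison; prespecifying it as a covariate would gain a little precision at no cost in patients

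*Protocol article*

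**What the plan says.** The Data analysis section of the protocol article describes an intention-to-treat comparison in two short statements: "First, the nifedipine and placebo groups will be compared" and "Relative risks and 95% confidence intervals will be calculated for the relevant outcome measures". No covariate is named. Neither adjusted nor unadjusted is said.

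The same section gives a role to four baseline factors, "cervical fibronectin status, presence of ruptured membranes, multiple pregnancy as well as cervical length at study entry", but only for subgroup and interaction tests. Gestational age at entry is not among them. The section on procedures and randomisation gives a 1:1 ratio and mentions no stratification factor. It also says that "At study entry baseline demographics, obstetric and medical history are recorded".

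Gestational age at entry is fixed by the eligibility criteria. Women between 26+0 and 32+2 weeks "who have not delivered after 48 hours of tocolytics and corticosteroids are eligible for participation". The Background describes adverse neonatal outcome as "strongly related to gestational age at delivery and declines from 77% at 24-27 weeks to less then 2% at 34 weeks and beyond".

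**The concern.** Entry spans 6 weeks and 2 days of gestation, within a period over which the document itself reports a steep fall in risk. The reported fall is by gestational age at delivery. Delivery cannot precede entry, so entry age bounds delivery age from below and should carry part of that prognostic information. It is available for all women and is measured before allocation, so it is a safe covariate.

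A comparison that ignores a prognostic baseline variable has a wider confidence interval than necessary. The trial is sized at 80% power with no stated margin. The same applies to two secondary outcomes. Gestational age at delivery equals entry age plus latency by arithmetic, and birth weight plausibly follows it.

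**Working it through.** **1. The plan's own figure.** Inputs from the Sample size section: 25% against 14%, two-sided 5% level, 80% power. The pooled-variance formula without continuity correction is

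n per arm = [1.960·√(2·p̄·(1−p̄)) + 0.842·√(p₀(1−p₀) + p₁(1−p₁))]² / (p₀−p₁)²,

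with p̄ = 0.195. This gives [1.960·√0.31395 + 0.842·√0.3079]² / 0.0121 = (1.098 + 0.467)² / 0.0121 ≈ 202.5. That rounds up to 203 per arm and 406 in total, an exact match. Power at 203 per arm is 80.1%. The trial was therefore sized without any covariate.

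**2. How strong could entry age be?** The document does not say, so this has to be assumed. Taking 77% at about 26 weeks and 2% at 34 weeks from the Background, the log-odds fall from 1.21 to −3.89, which is 5.10 over 8 weeks, or 0.64 per week. That is an odds ratio of about 0.53 per week of gestational age at *delivery*. Entry age is a diluted proxy for delivery age, so 0.53 is a practical limit on its strength.

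Dilution is likely. The Background says "Approximately 75% of women with a diagnosis of threatened preterm labour have not delivered after the first 48 hours" and that 65% are still pregnant at two weeks. If the two percentages share a denominator, 0.65/0.75 = 87% of women undelivered at 48 hours are still pregnant at two weeks. Passing the 0.53 gradient through assumed latencies gave roughly 0.6 to 0.7 per week for entry age.

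**3. Gain from adjustment.** Simulation with 4,000 trials per row and 203 women per arm. Entry age was assumed uniform over 26+0 to 32+2 weeks, the outcome logistic in entry age, and overall risks were held at 25% and 14%. The crude two-proportion test is compared with a relative risk standardised from a logistic model containing entry age. The equivalent N is 406 × (crude SE / adjusted SE)² on the log relative risk scale.

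| Assumed OR per week | Control risk at 26+0 and 32+2 | Power, crude | Power, standardised RR | Equivalent crude N |
|---|---|---|---|---|
| 1.0 | 25.0%, 25.0% | 80.6% | 80.1% | 407 |
| 0.9 | 31.5%, 19.2% | 80.7% | 80.9% | 409 |
| 0.8 | 39.2%, 13.7% | 80.1% | 80.4% | 416 |
| 0.7 | 48.0%, 8.9% | 80.7% | 82.3% | 430 |
| 0.6 | 57.5%, 5.2% | 81.4% | 84.0% | 452 |
| 0.5 | 67.2%, 2.6% | 81.0% | 87.6% | 484 |

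Monte Carlo error is about √(0.8·0.2/4000) = 0.6 point per power figure. The logistic test adjusted for entry age gave almost the same power (80.7%, 82.6% and 84.1% at 0.8, 0.7 and 0.6). Modified Poisson regression at odds ratios of 0.6 to 0.7 added about 1 to 3.5 points, with Monte Carlo error of about 1 point.

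**4. Chance imbalance.** With entry age uniform over 6.29 weeks, its SD is 6.29/√12 = 1.81 weeks. Under simple randomisation the difference in arm means has SE 1.81·√(2/203) = 0.18 weeks, so one trial in 20 differs by more than 1.96 × 0.18 = 0.35 weeks. The resulting shift in the risk difference, at 25% risk, is about 0.35 × |ln OR| × 0.1875 × (1 − R²), where R² is the share of control outcome variance explained by entry age. For OR 0.8 (R² 0.029) this is 1.4 points, and for OR 0.6 (R² 0.131) about 3 points, against an 11-point target.

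**The case against.** The strongest reply is that nothing planned is wrong. Under 1:1 randomisation the crude relative risk is a valid estimate and its test holds its level. The chance imbalance in step 4 is already reflected in the width of its interval, and a crude analysis matches the way the trial was sized. All of that stands, and it limits the point to efficiency.

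A second reply is that this is a condensed article and that covariates are often listed in a full protocol or analysis plan, neither of which is shown. This also stands in part. That the analysis is crude is inferred from the Data analysis and Sample size sections read together. The document does not declare it, and the words introducing the comparison leave room for further analyses. What remains is that the article did select baseline factors for its analysis and gave none of these roles to a variable that is known for everyone.

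A reader might infer three stronger claims that the document does not support:

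- **That the plan's estimate is biased.** It is not, for the reason above.
- **That the reported fall in risk, which "declines from 77% at 24-27 weeks to less then 2% at 34 weeks and beyond", measures the strength of entry age.** Those figures concern gestational age at delivery. The Background also names corticosteroids and transfer to a tertiary centre as strongly related factors and does not rank gestational age above them.
- **That six or seven points of power are being lost.** This needs an odds ratio of 0.5 per week, which would make entry age a stronger predictor than delivery age itself (about 0.53).

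**Conclusion.** The point holds as a free improvement of minor severity. As described, the main comparison uses no covariate, although a baseline variable linked to the outcome is available for every woman. For an assumed odds ratio of 0.8 to 0.6 per week of entry age, prespecified adjustment adds about 0 to 3 points of power at N = 406. That is equivalent to a crude trial of about 416 to 452 women. At 0.8 or weaker the power gain cannot be told from zero within simulation error.

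The size rests on three assumptions: the odds ratio range, entry age uniform across the eligible window, and an outcome logistic in entry age. No gain was calculated for gestational age at delivery or birth weight, because the document gives no spread for either.

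**What to change.** Prespecify as the primary estimate a relative risk adjusted for gestational age at randomisation as a continuous covariate, by modified Poisson regression with robust variance or by standardisation from a logistic model. Either route keeps the planned effect measure; an adjusted odds ratio would not. Report the crude relative risk as supportive. Use the same baseline covariate when comparing gestational age at delivery and birth weight. State that gestational age at delivery is not to be used as a covariate, because it arises after randomisation and may be changed by treatment. If the statistical analysis plan already says this, confirmation is enough.

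The cost is a sentence or two in the plan. Sample size and data collection are unchanged. It should be fixed before unblinding, because adjustment added after an imbalance has been seen would be data-driven.

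### Multiple pregnancies are enrolled, but the plan fixes no unit of analysis (woman or child) for the primary composite or its 25% and 14% rates, and names only plain relative risks for outcomes that siblings share

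*Protocol article*

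**What the plan says.** All of the following is in the Protocol article.

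- **Eligibility** (Participants/eligibility criteria): "Women with both singleton and multiple gestations are included". No expected share of multiples is given.
- **Randomisation** (Procedures, recruitment, randomisation and collection of data): "Randomisation is 1:1 for nifedipine or placebo". It takes place after the woman consents, so siblings always share an arm.
- **Primary outcome** (Outcome measures): "The primary outcome measure is neonatal mortality and a composite of neonatal morbidity". Every component is something that happens to a child: death, lung disease, brain injury, sepsis or necrotising enterocolitis.
- **Secondary outcomes** (same section): several belong naturally to the infant, such as birth weight and days on ventilation. One is expressly individual: "we will compare the number of days that each neonate surpasses outside the hospital". Gestational age at delivery, by contrast, belongs to the pregnancy.
- **Sample size**: the reduction is from 25% to 14%. "Using a two-sided test with an alpha of 0.05 and a power of 0.80", the plan concludes that "we have to randomise 406 patients (203 in each arm". The Abstract calls these 406 women, and the Interim analysis section also counts women.
- **Data analysis**: "Relative risks and 95% confidence intervals will be calculated for the relevant outcome measures". Multiple pregnancy appears in this section only as a subgroup factor with an interaction test.

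**The concern.** Twins share the allocated treatment and usually the gestational age at delivery, and the Background says adverse neonatal outcome depends strongly on gestational age. Their outcomes cannot be assumed independent. A standard relative risk with the number of neonates as denominator would count each sibling as a separately randomised unit, so its standard error would be too small.

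The unit also defines the endpoint. The risk that a given child is affected and the risk that a woman has at least one affected child are different quantities with different rates. The Sample size section takes two rates of neonatal morbidity and turns them directly into a number of women without linking the two. If the unit is chosen after the data are seen, two different primary results are on offer.

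**Working it through.** **1. The plan's own figure.** Inputs from the Sample size section: p1 = 0.25, p2 = 0.14, two-sided alpha 0.05, power 0.80. The mean rate is 0.195. Pooled two-proportion formula without continuity correction:

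n per arm = [1.960·√(2·0.195·0.805) + 0.8416·√(0.25·0.75 + 0.14·0.86)]² / 0.11² = (1.0982 + 0.4670)² / 0.0121 = 202.5, rounded up to 203.

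This gives 406 in total, an exact match (power 0.801). The formula has no clustering term, so it fits one independent outcome per woman.

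**2. If the composite is counted once per woman.** With 203 per arm and the planning rates, RR = 0.14/0.25 = 0.56. The standard error of log RR is √[0.86/(0.14·203) + 0.75/(0.25·203)] = 0.212, and the 95% CI is 0.369 to 0.849. Women are independent, so this interval is valid as it stands.

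**3. If outcomes are counted per child and siblings are ignored.** Assumptions, not in the article: a share f of women carry twins (higher-order multiples ignored), and the within-pair correlation is ρ. Then:

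- design effect DE = [(1 − f) + 2f(1 + ρ)]/(1 + f) = 1 + 2fρ/(1 + f)
- correct CI width relative to the naive one, on the log scale: √DE
- true type I error at nominal 5%: 2·[1 − Φ(1.96/√DE)]
- effective children per arm: 203(1 + f)/DE

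| f | ρ | DE | √DE | True type I error | Power, adjusted, 203 women per arm |
|---|---|---|---|---|---|
| 0.10 | 0.3 | 1.055 | 1.027 | 5.6% | 0.817 |
| 0.10 | 0.7 | 1.127 | 1.062 | 6.5% | 0.791 |
| 0.20 | 0.5 | 1.167 | 1.080 | 7.0% | 0.812 |
| 0.25 | 0.5 | 1.200 | 1.095 | 7.4% | 0.817 |
| 0.30 | 0.3 | 1.138 | 1.067 | 6.6% | 0.851 |
| 0.30 | 0.7 | 1.323 | 1.150 | 8.8% | 0.794 |

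Example at f = 0.25, ρ = 0.5: 203·1.25 = 254 children per arm. The naive CI for RR 0.56 is 0.386 to 0.812; the adjusted CI is 0.373 to 0.842.

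**4. Within the multiple-pregnancy subgroup.** If all members are twins, DE = 1 + ρ. A naive per-child test there has a true type I error of 8.6% at ρ = 0.3 (DE 1.3) and 13.3% at ρ = 0.7 (DE 1.7). The interaction test would use the same understated standard error for that stratum.

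**5. How far the two units differ.** Suppose 25% and 14% are per-child rates, with f = 0.25 and ρ = 0.5. The chance that at least one twin is affected is 1 − [(1 − p)² + ρp(1 − p)].

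- Control: 1 − (0.5625 + 0.0938) = 0.344, so the per-woman rate is 0.75·0.25 + 0.25·0.344 = 27.3%.
- Nifedipine: 1 − (0.7396 + 0.0602) = 0.200, so the per-woman rate is 0.75·0.14 + 0.25·0.200 = 15.5%.

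Putting 27.3% and 15.5% into the formula of step 1 with 203 women per arm gives power of about 0.83.

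**The case against.** A reader might infer that the plan treats siblings as independent. The article does not say so. It names no denominator, and a relative risk with a 95% CI can be computed per woman, or per child with clustered standard errors. What internal evidence there is leans towards the woman: 406 is a count of women, it comes from a formula for one outcome per woman, and the interim looks count women. The wording that singles out each neonate concerns one secondary outcome, a count of days, and does not settle the unit of the primary composite. On a per-woman reading, no type I error problem arises for the primary outcome. All of this stands, so the consequence can only be stated conditionally.

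A reader might also infer that sizing the trial in women makes the intervals too narrow or leaves the trial short of power. It does neither. Second twins add some information, and adjusted power is about 0.79 to 0.85 over the assumed range.

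Finally, this is a condensed article, and the choice between GEE and a mixed model is commonly left to the full protocol or analysis plan. That is fair for the variance method. It is less persuasive for the unit of the primary outcome, which defines the endpoint and gives the 25% and 14% their meaning. Nor does the per-woman reading cover outcomes that are naturally per infant, for which the article names only the plain method.

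**Conclusion.** The point holds in conditional form. The article enrols multiples, randomises women and measures events of the child, yet it fixes no unit for the primary composite or its planning rates and names only plain relative risks. A once-per-woman composite makes the primary analysis valid as stated. Any per-child analysis that ignores siblings should have intervals about 3% to 15% wider and has a type I error of about 5.6% to 8.8%; within an all-twin subgroup the error is about 8.6% to 13.3%. These figures rest on an assumed twin share of 10% to 30% (for the overall analysis) and a within-pair correlation of 0.3 to 0.7, neither of which the article gives. At the low end the effect is small.

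The documents do not support saying that siblings are analysed as independent, that the sample is too small, or that 25% and 14% are per-woman rates.

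**What to change.** Settle the following before outcome data are seen by arm:

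1. Define the primary analysis per randomised woman: at least one child with the composite event, with women as denominator. The plain relative risk and its 95% CI are then valid and match the 406.
2. Analyse every per-child outcome, including days outside hospital and any per-child version of the composite, with GEE or cluster-robust standard errors and the mother as cluster. Do the same for per-child analyses in the multiple-pregnancy subgroup and for its interaction test.
3. State, from their source, whether 25% and 14% are per-woman or per-child rates. They should not simply be declared per-woman to fit the 406.

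The cost is wording and slightly wider intervals for per-child outcomes. No new data are needed beyond the link between each child and its mother, and the sample size need not change.
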